**Monthly Sessions**		
Session 21: Preventing Relapse	Dental Care	Guided Imagery
Session 22: Staying on Top of Physical Activity	Sleep Habits	Social Support
Session 23: Stepping Up to Physical Activity	Domestic Violence	Sleep Strategies
Session 24: Balance Your Thoughts for Maintenance	Vaccines	Distraction Techniques
Session 25: Handling Holidays, Vacations, and Special Events	Women’s Health Take-Home Points	Stress Management Take-Home Points
Session 26: Final Session: Look Back and Looking Forward	Women’s Health Take-Home Points	Stress Management Reflection

^a^Behavioral weight loss

The stress management strategies are evidence-based and were selected to address stressors that adult Black females with obesity had reported as culturally salient barriers to weight loss in our preliminary studies [37] (Table 2). Stress management training will include cognitive, behavioral, and relaxation coping strategies guided by Kreuter’s framework for appropriate cultural adaptation of behavioral interventions, which uses five strategies: *peripheral, evidential, linguistic, constituent-involving, and socio-cultural* [38] (Table 3). Cognitive strategies such as challenging dichotomous thinking and making positive self-statements that have been shown to reduce stress [39] will be taught as one approach. Participants will receive instruction in evidence-based behavioral strategies [40] including time management, financial management, and distraction techniques (e.g., listening to music) [40, 41], as well as relaxation techniques such as diaphragmatic breathing, progressive muscle relaxation, guided imagery, and massage [39, 41, 42]. These evidence-based techniques will be linked with needs, values, beliefs, and culture of the target population (e.g., collectivism, racial pride, religiosity/spirituality) to provide culturally relevant strategies for stress management among Black females with elevated stress. While we are primarily focused on culturally-targeted stress management strategies, some elements of the cultural targeting, e.g., racial- and gender-concordant interventionists, will naturally be imbedded into the BWL portion of the intervention. Participants will also receive a voucher for a monthly Swedish massage from licensed therapists at a local spa; the therapists will follow a standardized protocol to minimize technique variability across participants.

**Table 2 Tab2:** Excerpt of results from formative assessments identifying stressors that are relevant to adult Black females and weight management

Sample Responses	Theme	Examples of Resulting Stress Management Enhancements
Q1. Taking care of everyone Q2. Child care as a single parent Q3. No time to eat right because I do for everyone else	Daily/Caregiver stress	-Benefits of massage -Time management -Social support/collectivism
Q1. Advancing in my career Q2. Job discrimination and being the only Black woman in the office	Work stress	-Challenging dichotomous thinking -Diaphragmatic breathing
Q1. Women don’t get the same chances as men Q2. I’m always worried about safety raising Black boys and being married to a Black man	Stigma, Discrimination, Bias	-Positive self-statements with pride in race and sex -Guided imagery
Q1. Paying for college as a single mother Q2. Not making as much money on jobs as men or white women Q3. Being healthy is expensive and hard for people with limited money	Financial stress	-Financial management and spiritual messages about provision
Q1. Trying to be in a good, happy relationship Q2. It’s hard for Black women to find a good Black man Q3. A lot of what I eat is just because of my husband	Relationship stress	-Distraction techniques -Meditation with focus on peace, spirituality, and pride

**Table 3 Tab3:** Alignment of stress management intervention with Kreuter’s framework for cultural appropriateness in behavioral interventions

Categories for enhancing cultural appropriateness	Stress management enhancements	Examples
Peripheral	Racial, sex-specific, and cultural concordance	-Race- and sex-concordant interventionist; culturally concordant images in stress management materials
Evidential	Race- and sex-specific statistics on topic area	-Black women report higher chronic stress than white women and tend to use coping strategies that exude strength, which may negatively impact health
Linguistic	Use of dominant native language of target group	-Written and verbal stress management training will be presented in English; race- and sex-concordance of interventionists will increase the likelihood of culturally consistent meaning of language
Constituent-Involving	Identification of culturally relevant stressors and use of direct quotes from formative assessments in materials	- Job and race/sex-related stress: “I am mostly stressed out by my job. It is already challenging and I am the only black woman in the office” - Financial stress: “As a single parent, it’s hard putting kids through college”
Socio-Cultural	Incorporation of stress management strategies that are relevant to the values, beliefs, and culture of the targeted population, including religiosity/spirituality, racial pride, collectivism, and perception of time	-Meditation that includes elements of spirituality (prayer, scripture) -Positive self-statements that include

Participant implementation of the stress management strategies will be monitored by a daily autogenerated text messaging prompt that will ask “Did you use any of the stress management strategies today that you have learned as a part of the RESET Study?” If the response is “yes,” participants will receive another prompt instructing them to describe the stress management strategy that was used. This will allow not only insights into the preferential engagement in the different strategies introduced and shed light on the stress coping strategies perceived as most useful by Black women engaged in weight control efforts but will also provide an index of participant skill enactment and treatment fidelity.

### BWL-alone

BWL-Alone will meet in 60-min group sessions which will present the same DPP-based lifestyle change curriculum and will be augmented with a 20-min session on general women’s health topics (e.g., breast health, dental care) as an attention placebo to account for any impact that attention from the interventionist might produce (Table 1). The total session time will be approximately 80 min. The use of women’s health topics as an attention control has been successfully used before in the BWL literature [43] and in our pilot study [24]. For the 20-min, women’s health-focused sessions, the interventionist will review and summarize the current literature and guidelines from reputable publicly available sources (e.g., Centers for Disease Control; National Institutes of Health). Stress management will not be addressed in these women’s health topics to avoid contamination.

### Intervention materials

Participants will receive written materials for each session, sets of measuring cups and spoons, and a food scale to assist with self-monitoring. Written materials will be emailed weekly, and other supplies will be distributed at the baseline assessment. Participants will track their weight, dietary intake, and activity in MyFitnessPal, an app-based self-monitoring smartphone program. Participants will also receive automated weekly texts prompting them to report a time in the past week when they used strategies discussed in the sessions (either stress or women’s health). For example, a BWL-Stress participant may record a stressful event and the coping strategy that she implemented. A BWL-Alone participant may document conducting a self-breast exam. These records will be collected weekly to serve as adherence and engagement data in analyses comparing the two intervention conditions.

### Treatment Fidelity and staff training

All interventionists delivering the group-based sessions will receive initial training and then meet weekly with the study PI to review issues or concerns and ensure consistent delivery of the intervention. All treatment sessions will follow a structured outline of content that will also be reviewed at the weekly meeting preceding each treatment session. Additionally, a random sample of treatment sessions (10%) will be audio-recorded for evaluation by research staff (EE) to ensure treatment fidelity. Corrective feedback will be provided to interventionists as needed.

## Interventionists

Group-based treatment sessions will be led by Black female master’s level staff trained in health behavior/health promotion with extensive experience in BWL interventions. Since racial concordance of interventionists and participants is neither positively nor negatively associated with weight loss outcomes for Black participants [44], and Kreuter’s framework suggests that these types of “peripheral strategies,” similar to “surface tailoring” as introduced by Resnicow et al. [45] can enhance credibility and acceptance of a group, racially- concordant interventionists will be used. The BWL-Stress and BWL-Alone groups will be led by different interventionists to minimize the risk of across-group contamination. Interventionists will be similar in terms of training and experience and will be trained to employ a similar style to minimize the potential for interventionist effect.

### Changes to the protocol due to COVID-19

Due to the COVID-19 crisis, the proposed in-person intervention from the initial protocol design has been adapted for implementation via Zoom. Activities from the DPP curriculum (e.g., food demonstrations) have been modified for the online format, and the number of site visits has been reduced to assessment visits only. Weigh-ins will only be conducted at assessments (four times per cohort) instead of the proposed 26 in-person intervention sessions and four assessment visits. Participants will be asked to weigh themselves weekly and record their weights within the MyFitnessPal app, where they will also be asked to self-monitor their dietary intake and activity. Intervention materials (i.e., worksheets and information sheets) will be emailed to participants prior to the intervention session. Participants will be asked to print their own materials. To further reduce site visits, participants will be asked to mail their saliva kits and activity monitors to a member of the study team for analysis. Non-monetary incentive benchmarks will be aligned with assessment visits instead of being spaced out throughout the duration of the study. Participants will track their dietary intake and physical activity using the MyFitnessPal app instead of a food and activity diary. Lastly, to foster a positive group dynamic, interventionists will be trained to engage participants via Zoom (e.g., using polls and online whiteboards), and participants will receive Zoom backgrounds for the sessions. All adjustments have been discussed in detail among the investigative team and in consultation with other experts. The decisions were made to use approached that will minimize any impact on scientific rigor. Modifications have been approved by the Scientific Review Committee (SRC) and Institutional Review Board (IRB).

### Assessment design and outcome measures

Data will be collected at baseline and months 4, 6, and 12. All assessments will be conducted by trained research staff who will undergo regular protocol-driven training and monitoring to ensure rigorous and unbiased data collection. Calibrated digital monitoring devices will be used for clinical measures (e.g., weight, height, blood pressure, blood glucose) to minimize error or bias. All study assessments will be conducted at Moffitt Cancer Center.

#### Primary outcome: anthropometry

Height and weight will be measured following a standardized protocol using a SECA 2-in-1 scale and stadiometer. Both measurements will be performed with participants’ shoes removed and wearing light clothing. BMI will be calculated from measured height and weight. Our primary outcome is 6-month weight loss. We will also examine weight loss at 12 months for maintenance outcomes.

#### Secondary outcomes

##### Stress

Participants’ perception of psychological stress will be assessed using the PSS-10 and STRAIN. The PSS-10 measures the degree to which an individual perceives life events to be stressful. Sample items include: “In the past month, how often have you felt that you could not cope with all the things that you had to do?” and “How often have you felt that you were unable to control the important things in your life?” Responses are on a 5-point Likert sale (0 = never to 4 = very often). Four items (e.g., “felt confident about ability to handle personal problems”; “I felt things were going my way”) are positively worded and will be reverse coded for analysis. Higher total scores correspond to greater perceived stress. The PSS-10 has been validated in diverse populations and demonstrated to have good internal consistency (α = 0.77) in a previous study conducted by our group among a similar population [46]. STRAIN is an instrument that measures cumulative exposure to life stress, with questions on acute life events, chronic difficulties, and early life stressors [28]. STRAIN contains approximately 220 total questions, with automated omission of questions that are inappropriate for the respondent’s demographic characteristics. STRAIN is structured with close-ended core questions about 55 distinct stressors related to major life domains (e.g., health, education, work, finances, housing, living conditions, intimate relationships, friendships, crime, etc.) and follow-up questions regarding the severity, frequency, timing, and duration of each stressor. A set of 20 lifetime stressor scores will be created based on STRAIN responses. Objective stress will be measured by salivary cortisol via SalivaBio Oral Swab (Salimetrics, LLC, Carlsbad, CA, USA) at baseline and 6-months to correspond with the primary study outcome of weight loss at 6 months. Participants will be provided with a Salimetrics Swab Saliva Collection Kit that includes 9 swabs and tubes. Participants will be asked to collect saliva upon waking and at 30- and 60-min after waking for 3 consecutive days. Participants will be asked to store the samples in their home freezer until they return the samples to our research team after completion at each time point.

##### Waist circumference

Waist circumference will be measured using a Gulick constant-tension spring-loaded tape device on bare skin at the end of a normal expiration at the natural indentation between the 10th rib and the iliac crest to the nearest 0.5 cm.

##### Blood glucose

Blood glucose will be assessed from a blood sample collected via fingerstick and read by a calibrated monitor (Roche Diagnostics).

##### Blood pressure

Blood pressure will be measured using standard procedures at rest, in duplicate, using a WelchAllyn blood pressure monitor at each assessment time point. Measurements will be averaged at each time point.

##### Energy intake

Energy intake will be assessed by 24-h dietary recalls conducted using the National Cancer Institute’s Automated Self-Administered 24-Hour Recall tool (NCI ASA-24). The NCI ASA-24 is drawn from the USDA’s Automated Multiple-Pass Method which uses the “gold standard” multiple-pass methodology. This web-based program allows researchers to enter dietary recall data via a respondent portal that is linked to a researcher site where data are saved for future download. The NCI ASA-24 uses Computer-Assisted Self-Interviewing (CASI) methodology to guide the respondent through multiple steps of recall, including meal-based quick list, meal gap review, detail pass (including quantity consumed), forgotten foods, and final review. Data will be quantitated to assess energy and nutrient intake, and average daily caloric intake will be the parameter of analysis. Each assessment will include a weekday and weekend day to account for eating variations.

##### Physical activity (PA)

PA will be assessed via activity monitors (i.e., Fitbit Inspire 2) worn by participants for 7 days. Participants will be instructed to position the activity monitor on their non-dominant wrist and to wear the device throughout the day. A valid day of data will be considered at least 10 h of waking wear time. These data will be used to estimate total weekly minutes of moderate-to-vigorous intensity PA. Self-reported PA will also be assessed with the Paffenbarger Physical Activity Questionnaire (PPAQ). Activity monitors provide objective information about total levels of activity, while the PPAQ provides additional details about the type and schedule of activities.

##### Treatment adherence

Treatment adherence will be assessed by the number of sessions attended and the proportion of days when self-monitoring of dietary intake is completed [24, 30, 47, 48]. Research staff will review and record self-monitoring on the MyFitnessPal app to provide data on self-monitoring adherence.

##### Treatment burden

Behavioral burden of treatment will be assessed with a 15-item survey measuring the burden of treatment, including behaviors of self-monitoring, dietary changes, maintaining physical activity, and the impact of treatment on social relationships, which will be administered at visits at month 6 and month 12.

### Retention

Several strategies will be implemented to promote retention among study participants. In addition to receiving a CDC-recognized BWL program at no cost to them, participants will be provided with the results of their assessments, including BMI, waist circumference, blood glucose, blood pressure, and PSS-10 score. We will also send birthday and holiday cards to remain connected to participants. To further promote retention, we will provide participants with monetary incentives for completing each of three follow-up data collection visits, with an escalating scale of reimbursement to maximize the acquisition of follow-up data, including $50 at month 4, $100 at month 6, and $150 at month 12. Participants will also receive non-monetary incentives, i.e., merchandise with the study logo, such as a water bottle for perfect attendance by month 4 assessment, for achieving milestones. Finally, the research team will foster relationships and rapport with participants, which will positively impact adherence and retention. The research team will also have a weekly review of attendance to discuss participants at-risk for loss and discuss targeted strategies for retention (e.g., troubleshooting transportation challenges or scheduling conflicts) to proactively limit attrition. If a participant misses two consecutive intervention sessions, a member of the research staff will reach out to them directly to identify and discuss any barriers that may be able to be addressed.

### Data management and security

Data will be entered into a custom-designed database through REDCap [49]. Relational logic checks such as out-of-range values and internal consistencies will be developed and run periodically. Statistical reports will be generated to examine the total number of participants screened, consented, and randomized on study entry and follow-up, as well as a summary of demographic and baseline characteristics.

### Statistical analyses

For the primary aim which compares BWL-Stress and BWL-Alone on 6-month weight loss outcomes, weight change (baseline weight subtracted from 6-month weight), will be tested using linear models and adjusted for known prognostic measures for weight loss such as age [50] and baseline weight. Model diagnostics, such as assessing normality of residuals and homoskedasticity, will be performed. If any assumption is violated, appropriate transformations (e.g., log) or analyses (e.g., quantile regression) will be performed. Follow-up analyses will be conducted to examine weight loss at month 12.

The secondary aim examines change in perceived, self-reported psychological stress, and will specifically examine changes in PSS-10 and STRAIN scores and cortisol by intervention group at month 6. Similar to Aim 1, change scores will be created and treated as continuous, and adjusted linear models and baseline outcome measure will be performed with appropriate diagnostics for model assumptions. Stress will also be examined at month 12 using data from the PSS-10.

For Aim 3, which examines whether the relationship between the intervention and weight change is mediated by perceived stress, energy intake, and physical activity, we will determine whether the relationship between each intervention condition and weight loss is mediated by perceived stress (as measured by the PSS-10), caloric intake, or physical activity [51]. Each potential mediator will be evaluated independently using a counterfactual approach [52]. As we are interested in multiple mediators which likely are not independent, we will use inverse odds ratio weighting (IOWR) to estimate the natural direct effect of BWL-Stress and BWL-Alone [53, 54]. This method first estimates weights by using logistic regression (to predict the dichotomous exposure variable) containing all mediators and confounders and creates an odds ratio for each participant. Next, the odds ratios (OR) are inverted (f (OR_i_) = OR_i_^− 1^) for each participant to create an IORW weight with standard BWL participants having weight 1. Direct effects of the intervention are estimated using weighted linear regression models including confounders and no mediators using IORW weights. The total effect of the intervention on weight loss is then estimated using an unweighted linear regression with the same confounders as the weighted analysis. The indirect effect is then estimated by subtracting the direct effect from the total effect. Confidence intervals for the effects are created using bootstrap methods. All analyses will be intention-to-treat. Baseline observation carried forward, which conservatively estimates a return to pre-treatment weight, will be used for participants without follow-up outcome measures for the primary outcome of weight. For participants missing data other than the primary outcome, we will perform multiple imputation as appropriate, as complete case analyses are known to be biased.

Missing data will be handled using multiple imputation by chained equations (MICE) with auxiliary variables identified using procedures from Enders [55]. Estimates from different imputed datasets will be combined using Rubin’s rules, and these will be integrated with inverse weighting mediation measures based on Stata code from previous similar work [55]. Multiple imputation is superior to complete case analysis if the missing complete at random assumption is violated. The likelihood of meeting the missing at random assumption will be bolstered with the use of auxiliary variables.

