Psychological stress is associated with weight gain over time and higher body mass index (BMI) [11–13]. In previous BWL interventions, individuals with higher stress at the start of the weight loss program went on to lose less weight than those with lower stress [14, 15]. Given that Black females report higher chronic stress than other groups [16], have a unique stress experience due to the intersection of race and sex [17], and tend to employ coping strategies that may be detrimental to health [18–22], the role of stress on weight control efforts may be particularly relevant for Black women. There is a well-established literature on stress reduction interventions that address racial/ethnic, health, and socioeconomic differences in stress exposure and stress-related outcomes [16], as well as observational relationships suggesting that high stress levels may contribute to enduring and increasing adiposity [11]. However, there remains a gap in the literature about whether adding a culturally-targeted stress management component to an evidence-based BWL intervention will produce greater weight loss than the standard intervention. A 2018 review [13] reported that only two small studies have investigated how adding stress management training to BWL programs affects weight loss: one reported significant positive effects among Greek women [23], and the other, conducted in a sample of Black women, reported encouraging trends but was underpowered to detect significance [24]. In addition, a randomized BWL program that tested the addition of mindfulness training for stress reduction in a predominantly (60%) White sample did not lead to greater weight loss, although it led to greater glucose control, a secondary outcome [25]. The participants of color attended fewer sessions in the mindfulness condition, and had less weight loss, again suggesting culturally tailored stress reduction is needed [26]. The purpose of this study is to examine whether a culturally-targeted, stress management-enhanced BWL intervention will improve weight loss and stress reduction among Black females in a fully powered randomized, controlled trial.

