### Sample size and power

While primary analysis will be adjusted for prognostic factors for weight loss, sample size was determined using an equal variance t-test. Preliminary data identified a 1.4 kg loss for Lifestyle alone and 2.7 kg loss for Lifestyle + Stress interventions, with standard deviations of 2.1 and 4.0 kg, respectively, yielding a Cohen’s d of 0.44 [24]. As these measures were taken at 3 months, and the current study is assessing 6-month weight loss, larger effects are likely; however, to reduce the likelihood of using an effect size which is too large [29], the study has been powered for a Cohen’s d of 0.35. This effect comes from assuming the above with both groups having a 4 kg standard deviation. Thus, with 85% power and a Type 1 error rate of 0.05, 148 participants are needed per group for a total of 296 participants. To allow for 10% attrition without loss of power, 340 participants (170 per group) will be enrolled and randomized.

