### Recruiting and screening eligible participants

Participants will be recruited from the Tampa Bay area through flyers, word of mouth, and small media (e.g., websites, clinical trials advertisements) using culturally appropriate recruitment materials designed to engage Black women. Established relationships between Moffitt Cancer Center and the Tampa Bay Community Cancer Network will also be leveraged to aid in the recruitment of community volunteers for this research study. Recruitment campaigns will be conducted across Years 2-5 of the project to enroll approximately 85 participants per each of four waves, allowing for delivery of at least four treatment groups per cohort (two BWL-Stress and two BWL-Alone groups) with approximately 21 participants per group. Based on a conservative estimate of a 35% recruitment yield obtained from our preliminary research [24, 30], we anticipate pre-screening approximately 970 individuals (~ 323 per year) to enroll 340 participants over four waves. Method of recruitment will be documented.

Interested individuals will initially be screened by telephone by research staff. Based on preliminary eligibility, individuals will be scheduled for a baseline visit to confirm eligibility and complete the informed consent process. Eligible participants will complete all baseline assessments prior to randomization. The random allocation sequence will be generated with computer-generated random numbers.

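### Women are treated in at least 16 groups nested within arm, but the sample size and primary model take them as independent; any within-arm group correlation makes the planned test anti-conservative

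*Protocol article*

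**What the plan says.** - **Delivery (Recruiting and screening eligible participants; Intervention).** Each of four waves enrols about 85 women, "allowing for delivery of at least four treatment groups per cohort (two BWL-Stress and two BWL-Alone groups) with approximately 21 participants per group". Each group has 26 sessions over a year. Sixteen weekly and four fortnightly sessions, 20 in all, fall before the 6-month primary endpoint.
- **Leaders (Interventionists).** "The BWL-Stress and BWL-Alone groups will be led by different interventionists to minimize the risk of across-group contamination". The steps against leader effects are similar training and style; none is an analysis step.
- **Sample size (Sample size and power).** "sample size was determined using an equal variance t-test", and "the study has been powered for a Cohen’s d of 0.35". The result is 148 per arm at 85% power and a 0.05 error rate, raised to 170 per arm for attrition. No ICC or design effect is given.
- **Primary analysis (Statistical analyses).** Weight change "will be tested using linear models and adjusted for known prognostic measures for weight loss such as age [50] and baseline weight". The diagnostics named are normality and homoskedasticity, and the remedies named are transformation or quantile regression. Aim 2 follows the same pattern. Aim 3 uses linear regressions with bootstrap intervals. No term for treatment group, interventionist or wave is mentioned, nor any cluster-robust method.

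**The concern.** Women who share a leader and a set of peers for six months of sessions are likely to have correlated weight change. Because the treatment groups are nested within arm, variation between groups feeds directly into the arm contrast. An ordinary linear model spreads that variation over 340 supposedly independent women, so its standard error is too small. The named diagnostics would not reveal this and the named remedies would not correct it.

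At stake is the primary p-value of a trial that the article calls fully powered, and the Aim 2 p-values with it. The error favours declaring the enhanced intervention effective. A later analysis plan could correct the model, but the 85% figure would still rest on a calculation with no allowance for grouping.

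**Working it through.** **Reproducing the plan's figure.** A two-sided equal-variance t-test at d = 0.35, alpha 0.05 and 85% power gives 147.55, so 148 per arm; power at 148 is 85.1%. The figure reproduces, under independence.

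**Inputs.**
- Groups: 4 waves × 4 groups = 16, 8 per arm. The text says at least four per wave, so this is the planned minimum.
- Group size: m = 170/8 = 21.25. All 340 are kept because missing weights are filled by carrying the baseline observation forward.
- Effect: d = 0.35, as in the plan.
- ICC: not in the document; assumed 0.005 to 0.05.

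**Formulas.**
- Design effect: DE = 1 + (m − 1) × ICC
- Type I error of the planned test: 2 × P(T > t_crit/√DE), with T on 338 df
- Power of a valid test: noncentral t with noncentrality 0.35/√(2·DE/170). The df are 16 − 2 = 14, or 16 − 2 − 3 = 11 if wave is a fixed effect.

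**Example, ICC 0.02.** DE = 1 + 20.25 × 0.02 = 1.405. Type I error: 1.967/√1.405 = 1.659, giving 9.8%. Noncentrality: 0.35/√(2 × 1.405/170) = 0.35/0.1286 = 2.72, giving 71.6% power on 14 df.

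| ICC (assumed) | DE | Type I error, planned test | Power, DE only (338 df) | Power, 14 df | Power, 11 df |
|---|---|---|---|---|---|
| 0 | 1.00 | 5.0% | 89.6% | 85.1% | 83.5% |
| 0.005 | 1.10 | 6.2% | 86.6% | 81.6% | 79.9% |
| 0.01 | 1.20 | 7.4% | 83.5% | 78.1% | 76.4% |
| 0.02 | 1.41 | 9.8% | 77.5% | 71.6% | 69.8% |
| 0.05 | 2.01 | 16.7% | 62.1% | 56.3% | 54.6% |

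The first row isolates the df penalty: with no correlation at all, moving from 338 to 14 df lowers power from 89.6% to 85.1%.

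**On the plan's own 148 per arm** (m = 18.5), ICC 0.01 / 0.02 / 0.05 gives type I error 7.1% / 9.1% / 15.2% and 14-df power 73% / 67% / 53%.

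**Simulation** (20,000 trials, 8 groups of 18 or 19 per arm). At ICC 0 / 0.01 / 0.02 / 0.05 the unadjusted t-test rejects a true null in 5.2% / 7.0% / 9.7% / 15.5% of trials. A test on group means stays between 4.9% and 5.2%, with power 80% / 73% / 68% / 53%.

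**The case against.** - **The size rests on an assumption.** The article gives no ICC, and at zero the planned test holds its 5%. This stands: only the direction for a positive ICC is certain.
- **The power figures mix two effects.** At ICC 0.005 the design effect alone leaves 86.6%, above the stated 85%; at 0.01 it leaves 83.5%. The t-test calculation also takes no credit for covariate adjustment. A reader might infer that 85% power is certainly missed. The documents do not show that for a very small ICC; they show only that grouping was not allowed for.
- **Calendar time.** A reader might count shared calendar time among the causes of inflation. Both arms have two groups planned in every wave, so wave effects cancel in the arm contrast. With wave variance only, the simulated type I error of the planned test is 4.6% to 4.9%. Omitting wave does not inflate the error.
- **Leaders.** A reader might expect a group intercept to remove leader effects. It cannot do so fully, because interventionists differ by arm and leader is partly confounded with arm.
- **Number and kind of groups.** Sixteen is a minimum; more and smaller groups would lower the design effect and raise the df. That groups keep fixed membership is inferred from the waves and numbered sessions, not stated.
- **Detail left to the analysis plan.** The df method and the bootstrap resampling unit commonly are, so the article's silence on them is not held against it. This does not rescue a stated model class and a completed power calculation that both assume independence.
- **Baseline stress.** The Background reports that "individuals with higher stress at the start of the weight loss program went on to lose less weight than those with lower stress", which may suggest adding PSS-10 as a covariate. That has nothing to do with correlation within groups and forms no part of this point.

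**Conclusion.** The point holds in conditional form. As written, the primary and Aim 2 tests are anti-conservative for any within-arm group ICC above zero, and the 85% power takes no account of grouping. With all 340 analysed in 16 groups, an ICC of 0.005 to 0.05 puts type I error at about 6% to 17%. Power of a valid test is about 82% down to 56% on 14 df, or 80% down to 55% on 11 df with wave fitted. These figures assume equal group sizes, the same ICC in both arms, d = 0.35 and no gain from covariates. The direction is firm; the magnitudes are only as good as the assumed ICC.

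**What to change.** 1. Make the primary and Aim 2 models linear mixed models with a random intercept for treatment group and Kenward-Roger or Satterthwaite degrees of freedom. Wave may be added as a fixed effect for precision, at a cost of about three between-group df.
2. Resample whole treatment groups in the Aim 3 bootstrap, so that all aims treat the grouping alike.
3. Restate power over a range of ICCs, showing the design effect and the df penalty separately. Do not enrol more.
4. State as a limitation that leader effects are partly confounded with arm.

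Settle this before outcomes are analysed, so that the choice is not post hoc. It changes analysis wording only and needs each woman's treatment group and wave in the dataset. The cost is wider intervals and a less favourable power figure.
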